### Feedback from therapists on their tele-health experience

Please score the below questions as per the scale shown and please give a brief comment and a suggestion/reason for all questions.

**Table d31e1717:**

**1: Very Poor**	**2: Poor**	**3: Average**	**4: Good**	**5: Very Good**

**Table d31e1731:**

Questions	1	2	3	4	5	Comments and/or Suggestions
1. Rate the effectiveness of the implementation of the tele-rehab						
2. Do you strive towards achieving the best physiotherapy practice while conducting tele-rehab?	Yes/No (Elaborate Please)					
3. How likely are you to recommend tele-rehab to other colleagues?	1	2	3	4	5	Comments and/or Suggestions
4. Name the two resources that will assist you in performing tele-rehab more efficiently.						
5. Do you feel that you are effective as a therapist during tele-rehab consultations?	1	2	3	4	5	Comments and/or Suggestions
6. Are you satisfied with your experience of tele-rehab overall?	1	2	3	4	5	Comments and/or Suggestions
7. Which skills (clinical and non-clinical) did you learn or develop to carry out tele- rehab more effectively?	Clinical: Non-clinical:					
8. Which of your skills (clinical and non-clinical) did you transfer (teach other staff) to aid in carrying out effective tele- rehab?	Clinical: Non-clinical:					
9. What protocols, procedures or logistics would help to provide more effective tele-rehab in future?						
10. Any other suggestions or comments?

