**Table d31e1575:**

1.	Did you enjoy the experience of tele-rehab for you and your child?	Yes	No	N/A	Comments and/or Suggestions		
2.	Do you feel like you learnt better how to help your child during tele-rehab?	Yes	No	N/A	Comments and/or Suggestions		
3.	What was difficult for you during the tele-rehab calls and treatment?	Yes	No	N/A	Comments and/or Suggestions		
4.	Was your culture and language respected during the calls and treatment?	Yes	No	N/A	Comments and/or Suggestions		
5.	Was the therapist’s attitude friendly and caring towards you?	Yes	No	N/A	Comments and/or Suggestions		
6.	Were you able to use any of the videos or pictures that were sent to you?	Yes	No	N/A	Comments and/or Suggestions		
7.	Were you given the chance to ask questions about your child’s treatment?	Yes	No	N/A	Comments and/or Suggestions		
8.	Where you given the right to refuse tele-rehab treatment?	Yes	No	N/A	Comments and/or Suggestions		
9.	Do you feel your child has benefitted from the advice and exercises given during tele-rehab?	Yes	No	N/A	Comments and/or Suggestions		
10.	How likely are you to recommend tele-rehab to another parent?	Very low	Low	Not sure	High	Very high	Comment and/or suggestions:

## Appendix 6

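### Therapist feedback item 3 asks how likely a recommendation is but is scored from Very Poor to Very Good, so its frequencies have no clear meaning (minor)

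*Protocol article*

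**What the plan says.** The instruction at the head of Appendix 6 (therapist feedback) reads "Please score the below questions as per the scale shown" and also asks for a short comment on every question. Only one scale is shown: 1 Very Poor, 2 Poor, 3 Average, 4 Good, 5 Very Good.

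Four of the ten questions are scored on it:
- Item 1: "Rate the effectiveness of the implementation of the tele-rehab"
- Item 3: "How likely are you to recommend tele-rehab to other colleagues"
- Item 5: "Do you feel that you are effective as a therapist during tele-rehab consultations"
- Item 6: "Are you satisfied with your experience of tele-rehab overall"

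Item 2 takes a Yes/No answer with elaboration. Items 4 and 7 to 10 are open text.

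In Appendix 5 (caregiver questionnaire), item 10 asks "How likely are you to recommend tele-rehab to another parent" and offers Very low, Low, Not sure, High, Very high. Caregiver items 1 to 9 offer Yes, No or N/A.

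Physiotherapist experience is part of the first listed objective. For the experience data, the Statistical analysis section plans frequencies and proportions, a two-sample proportions test on Yes/No responses, chi-squared comparisons, and grouping of the qualitative material into themes.

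**The concern.** A response label should answer the question beside it. Very Poor or Average is not an answer to how likely someone is to do something, so each therapist has to decide what the number means. A 3 on item 3 could stand for undecided, indifferent, or a view that the service itself is middling. Once the forms are collected, a table of counts cannot separate these readings.

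The four scored items carry most of the quantitative evidence on therapist experience. The only other closed question, item 2, asks about striving for best practice, which is not a rating of the experience. What is at stake is whether one of those four results can be interpreted. A reader is also likely to look at therapists' and caregivers' willingness to recommend side by side, and would find them on different labels.

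**Working it through.** The plan gives no figure to reproduce and no power or sample-size quantity is involved. The check matches each scored therapist question to the scale it must use, and then to its nearest caregiver question.

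| Therapist item | What it asks for | Fit with Very Poor to Very Good | Nearest caregiver item |
|---|---|---|---|
| 1 | A rating of implementation | Fits | No 5-point counterpart |
| 3 | A likelihood | Does not fit | Item 10, 5-point likelihood labels |
| 5 | Whether the therapist feels effective | Usable if read as a rating of own effectiveness | No 5-point counterpart |
| 6 | Whether the therapist is satisfied | Usable if read as a rating of the experience | Item 1, Yes/No/N/A |

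The caregiver question nearest to item 6 is "Did you enjoy the experience of tele-rehab for you and your child".

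**Counts.** Four items are scored (1, 3, 5, 6). The misfit is plain for 1 of 4 (item 3). Two more (items 5 and 6) are phrased as yes/no questions but carry a 1 to 5 score. Only 1 of 4 has a caregiver counterpart on a 5-point scale, and it is again item 3.

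**The parallel pair, point by point.** Item 3 against caregiver item 10:
- 1 Very Poor / Very low
- 2 Poor / Low
- 3 Average / Not sure
- 4 Good / High
- 5 Very Good / Very high

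Both run from unfavourable to favourable, so the order agrees. The labels differ at all five points. The midpoints also differ in kind, since Average is a level of quality and Not sure is a state of indecision. Caregiver item 10 shows that labels fitting a recommendation question were already at hand when the forms were written.

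**The case against.** The case for leaving the form alone has several sound parts.

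**Items 5 and 6 are readable as they stand.** A therapist can take them as ratings of own performance and of the overall experience, with 5 as favourable. This is accepted. For these two items the matter is tidier wording, and rewording them is optional.

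**No comparison is lost that was planned.** A reader might infer that three therapist items can no longer be set beside the caregivers' ratings because of their labels. The documents do not support this. Items 5 and 6 have no 5-point caregiver rating to be compared with, so new labels would not create one. The Statistical analysis section names no test of therapist against caregiver ratings, and the objective asks for each group's experiences.

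**The ambiguity is softened elsewhere.** Comments are requested for every question, much of the therapist evidence is qualitative, and the Methods and design section plans a pilot to find errors in the methodology. This helps interpretation. It does not give the tabulated counts for item 3 a defined meaning, and the mismatch is already visible on the printed form.

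**No numerical effect can be claimed.** A reader might work out that one therapist choosing Average moves the favourable share by 10 percentage points among 10 therapists (1/10) or 5 points among 20 (1/20). Those therapist numbers would be assumed, and 1/n is the weight of any respondent on any item. An undecided therapist would probably choose 3 under either set of labels, so the share scoring 4 or 5 need not move.

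**The caregiver midpoint is not an error.** Not sure could be called a don't-know answer placed inside a scale, but it can equally mean undecided. Moving it off the scale is a debatable preference.

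**Conclusion.** The concern holds for item 3. The question asks for a likelihood, the only labels supplied describe quality, and the caregiver form uses likelihood labels for the parallel question. The planned frequencies for that item will have no clear meaning, and the two recommendation results will be reported on different labels.

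Its size is one plainly mismatched item out of four scored items, in a descriptive part of the study. No planned test or formal comparison is shown to change. This is a minor instrument fix. The conclusion rests only on the printed forms, and assumes that therapists receive Appendix 6 as shown, with no separate labels for item 3.

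**What to change.** Print likelihood labels under item 3 of Appendix 6 that match caregiver item 10, keeping the 1 to 5 order: 1 Very low, 2 Low, 3 Not sure, 4 High, 5 Very high. Amend the instruction so that the Very Poor to Very Good scale applies to the other scored items only.

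Optionally, reword items 5 and 6 as requests to rate one's own effectiveness and one's overall experience, so that the existing scale answers them directly.

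The documents do not say whether any forms have been completed. If some have, report the old and new versions separately, because an answer given under quality labels cannot be relabelled afterwards.

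The cost is a small revision of one short form, with no extra data or staff. The Ethical considerations section reports that approval has already been received, so the change may need to be notified to the ethics committee.
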